## Abstract

**Background:**

With global population aging, functional disability has become a major public health and social care challenge. The integrated care model, centered on intrinsic capacity, aims to optimize functional abilities and improve health outcomes through systematic interventions. This approach offers innovative insights into long-term care for old patients with disabilities in institutional settings.

**Aims:**

To explore the effectiveness of an “Integrated Care for Older People (ICOPE)-Based Long-Term Care Intervention Program” compared to a control group and to assess participants’ perceptions of the program.

**Methods:**

This mixed-methods study will employ an explanatory sequential design, starting with a quantitative evaluation using a randomized controlled trial (RCT), followed by a supplementary qualitative study. The old patients with disabilities will be randomly allocated in a 1:1 ratio into the intervention group or the control group. The old patients with disabilities in the intervention group will participate in a 12-week “ICOPE-Based Long-Term Care Intervention Program,” and in the control group will maintain their routine life and standard care practices. Participant outcomes in both conditions will be assessed at pre-intervention (T_0_, week 0), post-intervention (T_1_, week 12), and 1 month after the intervention (T_2_, week 16), and a generalized linear mixed model will be used for analysis. The primary outcome is the change in intrinsic capacity, with the significance of the mean difference assessed to determine the intervention effect. In the qualitative part of this study, interviews will be conducted with old patients with disabilities from the intervention group at T_1_ to explore their experiences of receiving the intervention, and content analysis will be applied to the data collected.

**Discussion:**

This study will assess the effectiveness of an “ICOPE-Based Long-Term Care Intervention Program” for old patients with disabilities in nursing homes. If effective, it could provide a feasible and structured approach to improving long-term care quality in institutional settings.

**Trial registration:**

Identifier, ChiCTR2400094580.

## Highlights

A mixed-methods study to enhance the intrinsic capacity of old patients with disabilities in nursing homes through an ICOPE-based long-term care intervention program.Study population will include old patients with disabilities in nursing homes.The outcomes of the ICOPE-based long-term care intervention program will be evaluated using a comprehensive and detailed assessment based on the ICOPE intrinsic capacity screening tool proposed by the World Health Organization (WHO). This includes assessments of cognitive function, motor function, sensory function (vision and hearing), vitality, and psychological function.Blinding of participants and trainers will not be possible, increasing the risk of bias.

## Introduction

1

With the further acceleration of global aging, the number of old patients with disabilities is increasing rapidly (1). The old patients with disabilities are those whose daily living abilities are partially or completely lost for a prolonged period (over 6 months) due to physiological aging, pathological damage, or physical and mental disabilities (2). United Nations statistics indicate that over 46% of the global population aged 60 and above live with disabilities, and more than 250 million older adults endure moderate to severe disabilities (3). According to projections, the number of older adults with disabilities in China is expected to continue rising steadily. By 2030, the proportion of old people with disabilities is projected to exceed 57%, reaching more than 77.66 million (4). In the absence of effective prevention and control strategies, this figure is anticipated to surpass 70% by 2050 (4). In this context, nursing homes, as the primary living and care setting for old patients with disabilities, warrant particular attention regarding the issue of disability (5).

Despite the significant advantages nursing homes show in providing professional care services (6), they still face some pressing challenges. First, the fragmentation of services is a prominent issue (7). The health problems of older adults are complex and long-term, with chronic diseases and geriatric syndromes being common (8). Without coordinated interventions, these issues may lead to polypharmacy, hospitalization, or even death. Secondly, the care service model is singular. Long-term care services mainly focus on physical care and functional rehabilitation for old patients with disabilities (9), lacking a comprehensive consideration of their multidimensional health needs, such as in exercise, cognition, nutrition, and other aspects. This limitation not only affects the effectiveness of care but also hinders the overall health recovery of older adults (10), placing enormous pressure on the healthcare system and social care services. Therefore, it is crucial to explore comprehensive and integrated long-term care strategies.

In its Global Report on Aging and Health (11), the WHO introduced two key concepts: intrinsic capacity and functional ability. Intrinsic capacity refers to the overall physical and psychological abilities of an individual (12), while functional ability refers to the combination and interaction of an individual’s intrinsic capacity with their environment, reflecting their ability to perform various functions (13). A shift in older adult care involves moving from focusing solely on treating a specific disease or health issue to maximizing the intrinsic capacity of older adults throughout their life course (14).

The decline in intrinsic capacity is a key predictor of disability, with a significant correlation between the two (15–18). Numerous studies conducted in communities, nursing homes, and hospitals have shown that the decline in one or more dimensions of intrinsic capacity is closely associated with disability (15–18). The WHO has also emphasized the identification of conditions associated with the loss of intrinsic capacity, providing opportunities for interventions to slow, halt, or reverse the downward trend (19). Therefore, early assessment and intervention in the decline of intrinsic capacity are of great significance for optimizing long-term care services for old patients with disabilities.

Building on the WHO’s Global Report on Aging and Health (11), the WHO introduced the ICOPE framework in 2017 (14), which focuses on optimizing the functionality and intrinsic capacity of older adults to enhance their overall health. As the WHO states, the complexity of health issues in older adults requires health services to be provided in a more integrated manner, with the goal of maximizing or improving the intrinsic capacity of older adults and promoting their functional abilities (20). To operationalize this goal, the “ICOPE Handbook: Guidance for Person-Centered Assessment and Pathways in Primary Care” outlines a five-step care pathway for the assessment and management of declines in intrinsic capacity among older people: (1) Screening for possible declines in intrinsic capacity; (2) Comprehensive assessment of health conditions related to the decline in intrinsic capacity; (3) Development of a personalized care plan; (4) Ensuring referral pathways and monitoring of the care plan; (5) Community engagement and caregiver support. This systematic process provides a structured foundation for delivering integrated care in community.

Currently, practice-based projects centered around intrinsic capacity, at the heart of the ICOPE framework, are being gradually launched to improve the quality of care for older adults. These ICOPE practice projects have been implemented in multiple countries worldwide, including France (21) and South Korea (22), achieving significant results. In China, researchers such as Ma et al. (23) conducted a study on 976 middle-aged and older adults (aged 50–97) enrolled in the ICOPE-China project, using the ICOPE screening tool for intrinsic capacity assessments. The study found that 69.1% of participants showed a decline in intrinsic capacity, validating the tool’s effectiveness in identifying declines in the intrinsic capacity of older adults and providing valuable insights for the further development of older adult care in China. Overall, while domestic projects primarily focus on the initial screening of intrinsic capacity, there is still a lack of systematic research and practical application regarding the design and implementation of comprehensive care pathways and intervention programs, particularly for old patients with disabilities in nursing homes.

The main aim of this study is to explore the effects and the experiences of using “long-term care intervention program based on ICOPE for old patients with disabilities in nursing homes” in old patients with disabilities. An explanatory sequential design will be used, starting with a RCT investigating the impact of a long-term care intervention program on intrinsic ability (motor function, cognitive function, psychological function, sensory function, and nutrition) in a group of old patients with disabilities. Subsequently, qualitative surveys will be conducted to gain an in-depth understanding of participants’ subjective experiences of participating in this exergame intervention, in particular the benefits arising from the intervention as well as the influencing factors for participation, which will help understanding the mechanisms behind the therapeutic effects. This information will provide a basis for optimizing, refining, and promoting long-term care intervention program.

We hypothesis that participants in the long-term care intervention program group will experience an improvement of intrinsic ability, compared to those in the control group. Furthermore, we anticipate that these improvements will be maintained at 1-months follow-up.

## Methods

2

### Study design

2.1

This mixed-methods study will consist of an assessor-blinded, parallel-group RCT and a qualitative component. The design will align with the Medical Research Council’s guidance for the evaluation of complex interventions (24). An explanatory sequential design will be adopted, beginning with a quantitative, outcome-based assessment of treatment effects, followed by a qualitative investigation to explore participants’ perceptions of the intervention. The qualitative study will allow understanding the real experiences of old patients with disabilities in nursing homes participating in the intervention and the mechanisms behind the treatment (25). The study design is illustrated in Figure 1.

**Figure 1 fig1:**
[figure not shown]
Study design flowchart.

The study will be prepared in accordance with the Good Reporting of a Mixed Methods Study (GRAMMS) guidelines (26) and the Standard Protocol Items: Recommendations for Interventional Trials (SPIRIT) statements (27, 28). This trial was prospectively registered at Chinese Clinical Trial Registry (number: ChiCTR2400094580) on 25nd December 2024.

### Sample size and power calculations

2.2

In quantitative research, this study will use a completely randomized design for sample size estimation. A repeated measures ANOVA *F*-test in G*Power 3.1 will assess the main effect of the within-between interaction. Parameters will be set as follows: effect size = 0.25, *α* = 0.05, 1-*β* = 0.90. The correlation among the three repeated measures was set to *r* = 0. Note that this reflects a conservative approximation and any correlation larger than *r* = 0 would have reduced the required amounts of participants. Software calculations will determine a required 70 participants (35 per group). Accounting for a 20% attrition rate, the final sample size will be 42 per group, totaling 84 participants.

In qualitative research, purposive sampling will be used to select old patients with disabilities in nursing homes who have completed the 12-week intervention. Recruitment, interviews, and data analysis will be conducted sequentially in an iterative process until data saturation is reached, determining the final sample size (29).

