### Randomization, allocation and blinding

2.4

Participants will be randomly allocated to the intervention or control groups in a 1:1 ratio using computer-based permuted block randomization. The randomization sequence will be generated by an independent research coordinator, and the details of group allocation will be concealed on cards placed inside sequentially numbered, sealed opaque envelopes. Outcome evaluators, and data analysts will be kept blinded.

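### The 20% attrition allowance multiplies 70 by 1.2 instead of dividing by 0.8, so 84 enrolled leave about 67 completers and power of about 0.89 at r = 0, not 0.90 (minor)

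*Protocol article*

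**What the plan says.** All the figures stand in section 2.2 (Sample size and power calculations) of the protocol article. The test is given as "A repeated measures ANOVA *F*-test in G*Power 3.1 will assess the main effect of the within-between interaction", with parameters "effect size = 0.25, *α* = 0.05, 1-*β* = 0.90". The correlation is fixed by "The correlation among the three repeated measures was set to *r* = 0", which the section describes as conservative because any larger value would lower the number needed. The result is "Software calculations will determine a required 70 participants (35 per group"), and the enrolment target follows: "Accounting for a 20% attrition rate, the final sample size will be 42 per group, totaling 84 participants". Section 2.4 sets the allocation: "Participants will be randomly allocated to the intervention or control groups in a 1:1 ratio using computer-based permuted block randomization". The section does not write out the inflation formula and does not define attrition in any special way.

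**The concern.** An allowance for attrition should leave the required number of participants after the expected loss. Here the enrolment target equals the required number plus 20% of that number. That is not the same as a number from which 20% can be lost. The figure is the one the trial will recruit to, and a reader will take section 2.2 to mean that 20% loss is covered at 90% power. If the base of 70 has no slack, the plan falls below its own target at its own attrition rate.

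**Working it through.** **Inputs.** From section 2.2: effect size 0.25 (taken as Cohen's f), α = 0.05, target power 0.90, m = 3 repeated measures, r = 0, required N = 70, attrition 20%, enrolment 84. From section 2.4: k = 2 groups, 1:1. Assumed, because the article does not state it: sphericity (ε = 1).

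**Step 1: reproduce the base of 70.** For the within-between interaction the noncentrality is λ = f² × N × m / (1 − r), with df1 = (k − 1)(m − 1) = 2 and df2 = (N − k)(m − 1). At N = 70:

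- λ = 0.0625 × 70 × 3 = 13.125
- df2 = 68 × 2 = 136
- power = 0.904

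The smallest N that reaches 0.90 is 70. The base figure is therefore right, and it has no spare participants.

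**Step 2: reproduce the 84.** 70 × 1.2 = 84, and 35 × 1.2 = 42 per group. The stated figure is matched exactly by multiplication. Division gives 70 / 0.8 = 87.5, and 35 / 0.8 = 43.75, hence 44 per group and 88 in all.

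**Step 3: what 84 leaves at 20% loss.**

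- 84 × 0.8 = 67.2 completers (42 × 0.8 = 33.6 per group), about 3 short of 70.
- 84 leaves 70 only if no more than 14 are lost: 14 / 84 = 16.7%.
- 88 × 0.8 = 70.4, which meets the requirement.

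**Step 4: power at the numbers left (r = 0).**

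| Completers | λ | df2 | Power |
|---|---|---|---|
| 70 | 13.125 | 136 | 0.904 |
| 68 | 12.750 | 132 | 0.895 |
| 67 | 12.5625 | 130 | 0.891 |
| 66 (33 per group) | 12.375 | 128 | 0.886 |

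Against the target of 0.90, the shortfall is 0.9 points at 67 and 1.4 points at 66.

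**Step 5: sensitivity to r.** With the same formula and r > 0, λ is divided by (1 − r). Power returns to 0.90 at r of about 0.03 with 67 completers and at r of about 0.045 with 66. At r = 0.3 it is about 0.97 with either number, and the required N falls to 50. At r = 0.5 the required N is 36.

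**The case against.** The case for leaving the figure alone has three parts.

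- **The loss is small.** It is about one point of power, in a calculation whose effect size and attrition rate are both round planning values. This stands, and it is why the point is minor.
- **The plan is already conservative.** Section 2.2 sets r = 0 and says that a larger correlation would reduce the number needed. For the stated test that is correct. Repeated scores on the same residents over 16 weeks are unlikely to correlate at less than 0.05, although the article gives no value. This limits the consequence. It does not make the attrition step right: the plan derived 70 at r = 0 and then added a separate allowance for attrition, and it does not offer the conservative r as that allowance.
- **The analysis need not be restricted to completers.** The abstract and section 2.8 plan a generalized linear mixed model over T0, T1 and T2, which can use data from participants who leave after T1. Treating 20% attrition as 20% of the information lost is therefore a worst case. But the plan itself inflates for attrition and gives no calculation that credits partial data.

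A reader might go further and infer a larger loss for the primary outcome, by taking it as the change from T0 to T1 and finding power near 0.85 at 33 per group. The documents do not support that. The abstract names the change in intrinsic capacity as primary, without singling out T0 to T1. The calculation also needs an assumed pattern of effect over time that the article does not give. And under that pattern the same contrast reaches only 0.871 with the full 35 per group, so most of the gap to 0.90 would come from changing the test, and only about 2 points from the attrition step.

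**Conclusion.** The point holds, as a minor arithmetic error. On the inputs of section 2.2, an enrolment of 84, attrition of 20% and power of 90% cannot all be true. At 20% attrition about 67 participants complete and power for the stated interaction test is about 0.89, which is about 1 to 1.5 points below target. The enrolment of 84 covers 16.7% attrition.

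This rests on reading the effect size as Cohen's f, on sphericity, on r = 0 as stated, and on counting each dropout as fully lost. A true correlation of about 0.03 to 0.05 or more removes the shortfall. It would be wrong to conclude that the trial is materially underpowered because of this step. The base figure of 70 is correct, and no outcome or analysis is affected.

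**What to change.** Reword the last sentence of the sample size paragraph in section 2.2, for example: *84 participants (42 per group) allow for 16.7% attrition; with 20% attrition about 67 complete, and power is about 0.89 at r = 0.* This costs one sentence, a slightly less favourable statement and no further recruitment.

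If the sponsor wants 20% attrition and 90% power both to stand, the consistent enrolment is 88 (44 per group), which is 4 more participants than planned.

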### Eligibility and recruitment

2.3

Participants will be recruited from nursing home in Changchun, Jilin Province, China. The old patients with disabilities in nursing homes will be recruited through live lecture, poster promotion and official account by researchers and staff. Eligible subjects will be screened through face-to-face surveys. Inclusion criteria for participants will be: (1) Will be aged ≥60 years; (2) Will reside in a nursing home; (3) Will be classified as having mild to moderate disability according to the Ministry of Civil Affairs’ National Standard for Elderly Ability Assessment; (4) Will volunteer to participate in the study and sign informed consent. Participants will be excluded if: (1) Older adults with severe cognitive impairment or severe mental disorders who are unable to comply with the study procedures; (2) Older adults with severe hearing or visual impairments that prevent clear and fluent communication.

### Randomization, allocation and blinding

2.4

Participants will be randomly allocated to the intervention or control groups in a 1:1 ratio using computer-based permuted block randomization. The randomization sequence will be generated by an independent research coordinator, and the details of group allocation will be concealed on cards placed inside sequentially numbered, sealed opaque envelopes. Outcome evaluators, and data analysts will be kept blinded.

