The intervention group will participate in the study for a total duration of 16 weeks, comprising a 12-week intervention phase followed by a 4-week follow-up phase. The old patients with disabilities in intervention group will take part in the “ICOPE-Based Long-Term Care Intervention Program for old patients with disabilities in Nursing Homes” (Table 1), in addition to receiving the same routine care as the control group. The intervention program was designed to enhance physical, nutritional, psychological, cognitive, and sensory functions, as well as to provide comprehensive health education and guidance. It comprised the following six components: (1) Motor function: training incorporated resistance training, aerobic exercise, flexibility training, and balance training, with each session lasting 30–45 min, twice per week. (2) Nutrition: nutritional support was tailored to individual needs based on nutritional status assessments, ensuring a balanced diet and appropriate oral supplementation. (3) Psychological function: ① Problem-solving counseling or therapy, 30–45 min per session, once every 2 weeks; ② Behavioral activation with a reward system, 30–45 min per session, once every 2 weeks. (4) Cognitive function: computer-assisted cognitive training using the virtual supermarket training system, 30–45 min per session, twice per week. (5) Sensory function: ① Auditory training using cards, 30–45 min per session, once weekly; ② Visual training using a bouncy ball, 30–45 min per session, once weekly. (6) Health education and guidance: it was delivered through thematic education sessions, covering essential health topics, conducted once per week for 30–45 min. All intervention sessions will be conducted in the nursing home’s activity room to ensure accessibility and consistency for participants.

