However, this study will also face some challenges. First, many nursing homes face imbalanced resource and funding allocation, with some lacking the necessary equipment, technical support, and staff for the intervention (48). To address this issue, the research team plans to apply for special funding to support the project. Furthermore, the team will work to optimize the internal resource allocation of institutions and develop tailored solutions based on the specific circumstances of each facility. Second, the long-term care intervention program covers multiple health aspects, requiring caregivers to have advanced knowledge and skills. However, inconsistent training in some nursing homes limits the program’s effectiveness. To address this, we plan to develop a comprehensive training program, offer expert-led courses, and regularly assess caregivers’ performance. Thirdly, each old patients with disabilities have different health conditions and needs, and existing standardized intervention programs may struggle to address individual differences (42). To overcome this challenge, this study will develop flexible and personalized interventions, adjusting them according to each older adult’s health status and needs. Fourth, the scales used are self-reported measures, which can be subject to bias. Factors such as acute illness, changes in physical function, and stressful events can impact the accuracy of participants’ responses (49). Therefore, if conditions permit, objective indicators, such as physiological indicators, will be considered alongside self-reported measures, to reduce the bias of individual subjective feelings and improve the objectivity of the assessment. Fifth, this study may be subject to selection bias, as participants are drawn from specific nursing homes that may not fully represent the broader population of older patients with disabilities. To minimize this risk, we will seek to recruit participants from multiple institutions with diverse characteristics. Finally, the old patients with disabilities in the control group will maintain their routine life and standard care practices within the nursing home. While this mirrors real-world practice, the lack of an active or attention-matched control may overestimate the intervention’s effect due to non-specific factors like increased attention or support, and this may affect internal validity.

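### The number of nursing homes is not stated consistently, and the allocation as described makes no provision for more than one: a small loss of precision, not a bias

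*Protocol article*

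**What the plan says.** **Number of homes.** Section 2.3 says "Participants will be recruited from nursing home in Changchun, Jilin Province, China", with neither an article nor a count. Its next sentence is in the plural: "The old patients with disabilities in nursing homes will be recruited through live lecture, poster promotion and official account by researchers and staff". Section 2.5.3.1 is singular: "All intervention sessions will be conducted in the nursing home’s activity room". The Discussion is plural. It says that "participants are drawn from specific nursing homes that may not fully represent the broader population", and it answers this limitation with an intention: "we will seek to recruit participants from multiple institutions with diverse characteristics".

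**Allocation.** Section 2.4 randomizes individuals "in a 1:1 ratio using computer-based permuted block randomization". It refers to the randomization sequence in the singular and to sequentially numbered, sealed opaque envelopes. It names no stratification factor. Section 2.2 says that "this study will use a completely randomized design for sample size estimation".

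**Analysis.** Section 2.8 plans a generalized linear mixed model with group, time and their interaction. Age, frailty status and unspecified other variables are covariates where data and feasibility allow. Home is not named.

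**The concern.** The allocation as described suits a trial in one home. The Discussion points to several homes and uses them as the remedy for selection bias, so a limitation is answered by a design feature that the Methods do not describe.

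Blocks on one list shared by several homes balance the arms overall, but not within each home. The protocol itself suggests that homes can differ in ways that matter: it says that "inconsistent training in some nursing homes limits" the programme's effectiveness, and it mentions unequal equipment, technical support and staff. If arm and home are correlated by chance, the treatment effect is estimated less precisely, whether or not home is later put in the model. One numbered envelope sequence is also awkward to open in order at several sites. What is at stake is some precision and a clear account of the design. The validity of the comparison is not in question.

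**Working it through.** **1. The protocol's own figure.** Inputs from section 2.2: f = 0.25, α = 0.05, power 0.90, two groups, m = 3 measurements, r = 0, within-between interaction. The noncentrality is λ = f²·N·m/(1 − r), with df1 = 2 and df2 = 2(N − 2). At N = 70, λ = 0.0625 × 70 × 3 = 13.125 and power is 0.904. At N = 68 it is 0.895. The stated 70 therefore reproduces. The final size is 35 × 1.2 = 42 per arm, or 84. The 84 is taken as given here.

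**2. Assumptions not in the documents.** K equal-sized homes, residents of all homes mixed in order of entry, block size 4 (block size 6 was also run for 2 to 6 homes, with nearly the same results), and a range of home ICCs. Simulations used 3,000 runs per setting for 2, 3, 4 and 6 homes, and a separate set of 4,000 runs gave the 8-home figures.

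**3. How uneven homes can become with one list.** Chance that at least one home is split 60:40 or worse: 4 to 5% with 2 homes, 47 to 48% with 3, 70 to 71% with 4, 92% with 6. Chance of 70:30 or worse: 0.1% with 2, 3% with 3, 15% with 4, about 55% with 6, 89% with 8. In runs with 2 to 6 homes, the largest within-home arm difference averaged 3.6 to 5.5 residents with one list and 0 to 1.9 with a list per home.

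**4. Precision when home is in the model.** With one list, the expected R² of arm on home is (K − 1)/83. Relative efficiency is 1 − R², and the variance ratio (VR) is the efficiency with a list per home divided by the efficiency with one list. Power is Φ(3.2415/√VR − 1.960), scaled so that a list per home gives 0.90.

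| Homes | (K − 1)/83 | Efficiency, one list | Efficiency, list per home | VR | Power |
|---|---|---|---|---|---|
| 2 | 0.012 | 0.988 | 1.000 | 1.011 | 0.897 |
| 3 | 0.024 | 0.976 | 1.000 | 1.024 | 0.893 |
| 4 | 0.036 | 0.964 | 0.998 | 1.036 | 0.890 |
| 6 | 0.060 | 0.941 | 0.994 | 1.057 | 0.884 |
| 8 | 0.084 | 0.917 | 0.991 | 1.081 | 0.877 |

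For 4, 6 and 8 homes the extra variance corresponds to about 84 × 0.036 = 3, 84 × 0.057 = 5 and 84 × 0.081 = 7 residents.

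**5. Precision when home is left out.** With n1j and n0j the numbers in home j by arm, and n1 and n0 the arm totals, the variance is (1 − ICC)·4/N + ICC·Σ(n1j/n1 − n0j/n0)². For 2 to 6 homes, the ratio of one list to a list per home is 1.005 to 1.008 at ICC 0.01, 1.03 to 1.04 at 0.05, 1.05 to 1.08 at 0.10 and 1.12 to 1.18 at 0.20. Power of 0.90 becomes about 0.90, 0.89, 0.88 and 0.85 to 0.87.

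**6. Where the loss vanishes.** With one home it is nil. If homes enrol one after another, imbalance is limited to part of a block at each changeover, and the loss is close to nil.

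**The case against.** The strongest objection is that much of this rests on silence. Section 2.4 does not say that one list serves all homes or that the list is unstratified. The completely randomized design in section 2.2 is named for the sample size estimate, not as the allocation rule. A condensed article may leave strata, block sizes and the layout of lists to the full protocol. This stands: a reader might infer a single unstratified list, and the singular sequence fits that reading, but the documents do not prove it. It is equally tempting to read section 2.3 as committing to one home. It gives no count, its next sentence is plural, and the Discussion states only an aim to seek several institutions.

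The remarks on equipment, staff and training concern nursing homes in general, and standardized training is planned (section 2.7). No variance between homes is given.

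The size is also modest. The tested effect is group by time, so stable differences in level between homes largely cancel, and the ICC figures above are upper-end. Differences in delivery could still affect change over time and need not cancel. The r = 0 in section 2.2 is declared conservative. At an assumed r = 0.5, N = 36 would reach 0.90 power, and with 70 analysed the 8-home loss moves power only from 0.997 to 0.995.

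None of this removes the inconsistency over the number of homes, or the fact that the allocation as described provides nothing for the multi-home plan.

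**Conclusion.** The point holds as a minor one. Sections 2.3 and 2.5.3.1 and the Discussion do not agree on whether one or several homes take part. If there are several, allocation stratified by home would improve on what section 2.4 describes.

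The gain is small. With home modelled, interleaved entry and 84 residents, one list costs about 1% in variance with 2 homes and 8% with 8, or roughly 0.3 to 2.3 power points from 0.90 at r = 0. If home is left out, the cost for 2 to 6 homes is similar at ICC 0.05 to 0.10 and reaches 3 to 5 points only at ICC 0.20. The number of homes, their sizes, the order of entry, the block size and the ICC are all assumptions.

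A reader might go further and infer that some homes will end up mostly in one arm, so that home differences confound the result. The documents do not support that. Residents are randomized individually, chance imbalance within homes leaves the comparison unbiased, and a 70:30 split is rare with 2 or 3 homes.

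**What to change.** Reconcile sections 2.3 and 2.5.3.1 and the Discussion on the number of homes.

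- **If more than one:** amend section 2.4 so that the independent coordinator generates a separate permuted-block list, with randomly varied block sizes, and a separate set of numbered envelopes for each home. Name home as a factor in the mixed model in section 2.8.
- **If only one:** say so in section 2.3, and remove the multi-institution statement from the Discussion.

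The cost is a sentence in each section and one list per home, with no extra residents. It should be settled before enrolment, because later adjustment for home cannot fully recover the lost balance. One small downside is that lists in small homes are easier to predict, in a trial where participants and trainers are not blinded. Varied block sizes limit this.
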